**Methods:**

This is a stratified, cluster randomized controlled trial conducted in Guangdong Province, China. Schools will be stratified by regional economic development level and randomly assigned to either an intervention or control group. The intervention group will receive annual dental examinations, biannual FV applications, and oral health education. The control group will receive standard annual examinations and comparable oral health education. Participants will be students aged 5 to 22 years enrolled in selected special education schools. Baseline assessments and 12-month follow-ups will include oral examinations and questionnaires assessing oral health knowledge, attitudes, and behaviors. The primary outcome is the difference in caries prevalence between the intervention and control groups at follow-up. Secondary outcomes include changes in oral hygiene behaviors and caregiver knowledge. Data will be analyzed using multivariable regression models adjusting for potential confounders and clustering effects.

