### Intervention and Control

The intervention group will receive 2 professionally administered FV applications. Applications will occur at baseline (month 0) and at 6 months, using Duraphat (Colgate-Palmolive Company) varnish, which contains 5% sodium fluoride by weight, equivalent to 22,600 parts per million fluoride ions [16,17]. The varnish will be applied to all erupted tooth surfaces by trained dental professionals under standard infection control procedures, including hand hygiene, appropriate personal protective equipment, and the use of single-use disposable materials to prevent cross-contamination, in accordance with Centers for Disease Control and Prevention guidelines for portable dental care [18]. A brief oral examination will be conducted prior to each session to confirm eligibility for varnish application. Prior to application, the teeth will be cleaned with sterile gauze and isolated with cotton rolls for moisture control [19]. The tooth surfaces will then be dried with gauze, followed by the application of 0.40 mL of 5% sodium fluoride varnish [20]. Concurrently, oral health education will be provided to parents and teachers of students. These educational sessions will be delivered during the school visits in which varnish applications occur. Content will include basic oral hygiene practices, the importance of fluoride in caries prevention, dietary advice, and strategies for supporting children with disabilities in maintaining oral health.

The control group will receive standard care, consisting of annual oral health examinations and oral health education. These educational components will be delivered during routine school visits using the same materials and format as in the intervention group, ensuring comparability of educational exposure between groups. However, no FV will be applied in control schools during the study period. The overview of the study is shown in Figure 2.

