### Study Outcomes

The primary outcome of this study is the prevalence of dental caries among students at 12 months following the intervention. Dental caries will be assessed through clinical oral examinations using the decayed, missing, and filled teeth index (DMFT) for permanent and primary dentition, respectively. These examinations will be conducted in accordance with the national standardized child oral health survey protocol used in China. Briefly, trained and calibrated dental professionals will perform tooth-level examinations using disposable dental mirrors and probes under natural or portable lighting. Dental status for both primary and permanent teeth, including caries experience and related conditions, will be recorded. Examinations will take place in a designated room with adequate lighting [21]. Children will be assessed while seated [22], and wheelchair users will remain in their own wheelchairs. Two familiar teachers or school support staff will attend to assist with communication and comfort [23]. A trained dentist will conduct the examination, and a trained nurse will record the number of decayed, missing due to caries, and filled teeth per child. The blank recording form is provided in Figure 3. To minimize measurement bias, examiners conducting the follow-up assessments will be blinded to the school allocation status.

Secondary outcomes include (1) oral hygiene status (eg, presence of plaque and gingivitis), assessed using gingival health indicators and plaque indices; (2) changes in oral health–related knowledge, attitudes, and practices (KAP) among students, parents, and teachers, measured using a structured questionnaire adapted from the Third National Oral Health Survey [24].

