Baseline assessments will be conducted prior to intervention implementation, with follow-up occurring 12 months later. Oral examinations will be performed on-site in schools, with each child examined in a standardized manner. KAP questionnaires will be administered to parents and teachers at both baseline and the end of follow-up. All data will be collected using the Wenjuan Star platform (Shanghai Zhongyan Network Technology Co Ltd) or through paper-based questionnaires with double data entry, depending on the logistical feasibility at each study site. Data from paper questionnaires will be manually entered into the electronic system by trained students at the university. Details of the information collected are shown in Table 1. Monitors appointed by the trial sponsor will oversee trial implementation to ensure protocol compliance and data accuracy (Multimedia Appendix 1).

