### Statistical Analysis

All data will be entered into a centralized electronic data capture system with built-in logic checks to ensure completeness and internal consistency. Statistical analyses will be conducted using Stata (version 18.0; StataCorp LLC). Descriptive statistics will first be generated to summarize baseline characteristics of participants in both intervention and control groups, including means, SDs, proportions, and frequency distributions.

Comparative analyses between groups will be conducted on an intention-to-treat basis. Participants will be analyzed according to their randomized group, regardless of receipt of FV. For descriptive and unadjusted comparisons between groups, chi-square tests will be used for categorical outcomes (eg, caries prevalence). For continuous variables, independent-samples *t* tests will be used for normally distributed data, and nonparametric tests (eg, Mann-Whitney *U* test) will be applied for skewed distributions. Paired comparisons (eg, baseline vs 12-month follow-up) within groups will use paired *t* tests or Wilcoxon signed-rank tests as appropriate.

To evaluate the effectiveness of the intervention while accounting for potential confounders and cluster randomization in the primary analysis, mixed-effects logistic regression will be used for binary outcomes, such as caries presence, and mixed-effects linear regression for continuous outcomes, such as the number of decayed teeth [27]. Models will adjust for relevant covariates, including age, sex, socioeconomic status, and baseline oral health status. Multiple imputation with chained equations will be applied to handle missing covariate data. Cluster effects will be accounted for using robust SEs or multilevel modeling, as appropriate. Effect estimates will be presented as adjusted odds ratios or mean differences with 95% CIs. All hypothesis testing will be 2-sided, with a significance level set at *P*<.05. Sensitivity analyses, including subgroup analyses by economic region, will be conducted to assess the robustness of the findings.

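### The planned within-arm before–after tests use neither the randomised control nor the school clustering, so they cannot support the secondary claims about change; the primary caries analysis is unaffected

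*Protocol article*

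**What the plan says.** The Statistical Analysis section lists simple unadjusted tests and ends that list with: "Paired comparisons (eg, baseline vs 12-month follow-up) within groups will use paired" t tests or Wilcoxon signed-rank tests. It sets a two-sided 5% level for all hypothesis testing and gives these within-arm tests no descriptive-only role.

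Some secondary outcomes are worded as changes. The Abstract says: "Secondary outcomes include changes in oral hygiene behaviors and caregiver knowledge". Study Outcomes lists "changes in oral health–related knowledge, attitudes, and practices (KAP) among students, parents, and teachers".

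Three features of the design bear on what a before–after difference means:
- Age and dentition. The Abstract says: "Participants will be students aged 5 to 22 years enrolled in selected special education schools". Study Outcomes says: "Dental status for both primary and permanent teeth, including caries experience and related conditions, will be recorded".
- Education in both arms. For the intervention arm, Intervention and Control says: "Concurrently, oral health education will be provided to parents and teachers of students". The control arm's education is delivered "using the same materials and format as in the intervention group, ensuring comparability of educational exposure between groups".
- Interval. Study Outcomes says: "Baseline assessments will be conducted prior to intervention implementation, with follow-up occurring 12 months later".

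The next paragraph of Statistical Analysis assigns effectiveness to mixed-effects logistic and linear models. These compare the arms, allow for clustering, and adjust for age, sex, socioeconomic status and oral health at baseline.

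**The concern.** A paired test inside one arm asks whether that arm changed over a year. It does not ask whether varnish changed it. Over 12 months, primary teeth are shed, permanent teeth erupt and become at risk, and caries experience accumulates in either arm. KAP and hygiene scores can move because both arms are educated. Parents and teachers also complete the KAP questionnaire at both visits.

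The tests as named also take students as independent, although whole schools are randomised and the sample size allows for clustering.

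The secondary claims are at stake. Hypothesized Findings in the Discussion expects the intervention to improve parents' and teachers' KAP scores significantly, although the education is meant to be the same in both arms. A significant KAP gain within the intervention arm would seem to confirm this even if the control arm gained as much. Likewise, a result that is significant in one arm and not in the other is not a comparison of the arms.

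**Working it through.** **1. The plan's own figures (Sample Size).** Inputs: 60% versus 40%, z values 1.96 and 1.28, school size m = 150, intracluster correlation (ICC) 0.02, 10% dropout.
- n = (1.96 + 1.28)² × (0.24 + 0.24) / 0.20² = 125.97, so 126 per group.
- Design effect = 1 + 149 × 0.02 = 3.98, and 126 × 3.98 = 501.48, so 501.
- 501 / 0.90 = 556.7, so 557 per group and 1114 in total.

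These agree with the article. The point does not dispute them.

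**2. Type I error of the paired test when there is no change at all.** If change scores are correlated within schools, the true variance of the mean change is about DE = 1 + (m − 1) × ICC times the variance that the test assumes. The actual two-sided error is then 2 × [1 − Φ(1.96 / √DE)].

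Assumptions: the article gives an ICC of 0.02 for its caries calculation and none for change scores. The 92 students per school comes from 1114 / 12 = 92.8, rounded down.

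| ICC of change | m | DE | 1.96/√DE | Type I error |
|---|---|---|---|---|
| 0 | any | 1 | 1.96 | 5% |
| 0.01 | 92 | 1.91 | 1.418 | 16% |
| 0.01 | 150 | 2.49 | 1.242 | 21% |
| 0.02 | 92 | 2.82 | 1.167 | 24% |
| 0.02 | 150 | 3.98 | 0.982 | 33% |

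A simulation (4,000 trials per setting, 7 versus 5 schools, 92 students per school, ICC 0.02, no change in either arm) gave 25.9% in the intervention arm and 24.6% in the control arm. A between-arm t test on school means rejected in 5.5%.

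**3. What the test shows when both arms change equally and varnish does nothing.** Take 501 students per arm, treated as independent, with a common change d in SDs of the individual change. The sizes of d are assumptions; the article gives none. The first probability, p, is from the noncentral t distribution with 500 degrees of freedom. The second is p(1 − p).

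| d | Significant in a given arm | Significant under varnish, not under control |
|---|---|---|
| 0.05 | 20% | 16% |
| 0.10 | 61% | 24% |
| 0.15 | 92% | 7.5% |
| 0.20 | 99% | 0.6% |

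The middle column is power to detect a real change, not an error rate. It shows that a significant within-arm result is compatible with no varnish effect. In the simulation with ICC 0.02 and d = 0.10, the intervention arm was significant in 64% of trials and the two arms disagreed in 50%, while the between-arm test rejected in 4.9%.

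These figures concern outcomes measured on students. The number of teachers is not given, so they do not carry over to teacher KAP.

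**The case against.** The strongest reply is that these tests have a minor role. They close a paragraph of simple comparisons, and the next paragraph gives effectiveness to between-arm mixed models. A 12-month comparison adjusted for baseline is the standard analysis of change, and for plaque and gingival scores the planned adjustment for oral health at baseline can supply it. The primary outcome is caries prevalence, compared between arms. All of this stands.

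Two stronger readings are therefore not supported. A reader might infer that varnish will be judged by the paired tests; the article nowhere says so. A reader might also infer that the paired test is the only planned analysis of change; the mixed models contradict that.

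It is also fair that the drift sizes are assumed and that the net direction is unknown: shedding of carious primary teeth lowers primary scores while accumulation raises permanent ones. Education reaches parents and teachers in the intervention arm, so it bears on KAP and hygiene more directly than on students' teeth. In the Discussion, the expectations for caries and hygiene read as comparative; only the KAP sentence is open to a within-arm reading.

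Finally, a condensed article may leave the labelling of within-arm results to an analysis plan. That reply carries less weight, because the article itself fixes the tests and the significance level and sets no limit on their interpretation.

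**Conclusion.** The point holds for the secondary outcomes. Followed as written, the plan produces within-arm P values that ignore the control arm and the schools. Their type I error would be about 24% to 33% if change scores had an ICC of 0.02, with 92 to 150 students per school. It would be lower with a smaller ICC and 5% with none. Even with clustering handled correctly, within-arm significance would not isolate varnish, because ageing, changing dentition and education also act in the arm.

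The primary caries analysis and the planned between-arm effect estimates are untouched. One narrow gap remains in the valid analysis: the planned adjustment for baseline oral health may not cover the baseline of each KAP score. This is a free improvement, not a flaw that threatens the main result.

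**What to change.** In Statistical Analysis, replace the sentence on paired tests with a statement that within-arm change will be shown as means and proportions without P values.

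Add that each secondary outcome declared or interpreted as a change (KAP, plaque and gingival scores) will be tested only by the between-arm difference at 12 months. Use the mixed model already planned, with school as the cluster and that outcome's own baseline value as a covariate. For KAP, name the baseline score explicitly. The article has parents and teachers complete the questionnaire at baseline and at the end of follow-up, so the values will exist for them.

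The cost is one or two sentences and no new data. According to the Abstract, data analysis had not started, so the change can be made before results are known. The only downside is fewer P values.

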Feeding behaviors	
Selective eating	Never to always (5-point scale)
Texture or color sensitivity	Never to always (5-point scale)
Food rituals	Never to always (5-point scale)
Disruptive mealtime behaviors	Never to always (5-point scale)
Food refusal behaviors	Never to always (5-point scale)
Oral health examination variables	
Caries type (eg, no caries, crown caries, filled with/without caries), primary vs permanent teeth	A: no caries; B: crown caries; C: filled with caries; D: filled without caries; E: missing due to caries; X: missing for other reasons
Tooth trauma type	Trauma types: enamel crack, enamel fracture, crown-dentine fracture, pulp exposure, avulsion, other
Crown discoloration	+; –
Tooth mobility	+; –
Presence of fistula	+; –
Tooth eruption stage	One-third; two-thirds; full
Presence of supernumerary teeth	Yes; no
Presence of fissure sealant	Yes; no
Presence and type of dental fillings	Yes; no (type noted)
Missing teeth due to caries or other reasons	Yes; no (reason noted)
Exposure of pulp in traumatic crown fractures	Yes; no
Periodontal condition measured using plaque index and gingival index	Clinical description

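### The example count outcome, number of decayed teeth, mixes new caries with treatment and tooth shedding; a tooth-level new-caries increment would fit the trial's aim better

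*Protocol article*

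**What the plan says.** The Study Outcomes section makes the primary outcome binary: "The primary outcome of this study is the prevalence of dental caries among students at 12 months following the intervention". Caries is assessed "using the decayed, missing, and filled teeth index (DMFT) for permanent and primary dentition, respectively", and at each examination "a trained nurse will record the number of decayed, missing due to caries, and filled teeth per child". The secondary outcomes listed there are oral hygiene status and knowledge, attitudes and practices. No caries count is among them.

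The Statistical Analysis section assigns mixed-effects logistic regression to binary outcomes and "mixed-effects linear regression for continuous outcomes, such as the number of decayed teeth". This is the only caries count the article names for modelling. The models adjust for age, sex, socioeconomic status and baseline oral health. The same section plans paired within-group comparisons of baseline with 12 months.

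Table 1 codes each tooth as A (no caries), B (crown caries) or one of "C: filled with caries; D: filled without caries; E: missing due to caries; X: missing for other reasons".

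Under Intervention and Control, varnish is applied at months 0 and 6, and "A brief oral examination will be conducted prior to each session", for the purpose of confirming eligibility. Control schools have annual examinations. The Hypothesized Findings section expects fewer new lesions in the varnish arm.

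**The concern.** Varnish is meant to prevent new lesions. The decayed component alone is a stock of currently untreated decay: new disease adds to it, and treatment and natural tooth loss take from it. It matches neither the index named in Study Outcomes, which also counts filled teeth and teeth missing due to caries, nor the hypothesis, which is about new caries.

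At ages 5 to 22 many participants are shedding primary teeth, so part of the stock will disappear within 12 months without any prevention. A new lesion that is filled before month 12 is never counted. If a mean difference or a within-arm change in this count is reported as caries prevented, the reader cannot tell how much of it is prevention.

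**Working it through.** **1. How a tooth leaves the count under Table 1.** A tooth coded B at baseline can become:

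- D, when filled with no remaining caries;
- E, when extracted because of caries;
- X, when shed. This is an inference: Table 1 defines X only as missing for other reasons and does not mention shedding.

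Each of these lowers the number of decayed teeth. A filled tooth that still has caries is coded C and need not leave the count.

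**2. The article's own figure.** No figure is given for a caries count. The sample size rests on prevalences only, and it reproduces:

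- (1.96 + 1.28)² × (0.24 + 0.24) / 0.20² = 125.97, so 126 per group;
- design effect 1 + 149 × 0.02 = 3.98, and 126 × 3.98 = 501.48, given as 501;
- 501 / 0.90 = 556.7, so 557 per group and 1114 in total.

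Nothing in this point changes these numbers.

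**3. Bookkeeping for the count.** Let D0 be decayed teeth at baseline, N the new lesions in control, r the share of baseline decay cleared, and s the share of new lesions cleared. Then

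D12 = D0 × (1 - r) + N × (1 - s).

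Assumed, not from the documents: D0 = 2, N = 0.5 or 1.0. The preventive effect is set at 37%, the upper figure that the Introduction cites for primary teeth. The true difference in new lesions is then -0.37 × 0.5 = -0.185 or -0.37 × 1.0 = -0.37.

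*Within the control arm, s = 0.* The change is N - r × D0.

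- N = 0.5: from 0.5 - 0 = +0.5 (r = 0) to 0.5 - 0.5 × 2 = -0.5 (r = 50%).
- N = 1.0: from +1.0 to 1.0 - 1.0 = 0.0.

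The same number of new lesions can thus appear as worsening, no change or improvement.

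*Between arms, equal r, s = 0.* The D0 × (1 - r) term cancels. The difference stays at -0.185 or -0.37 for every r.

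*Between arms, equal s.* The difference is the true effect × (1 - s).

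- N = 0.5: -0.185 × 0.90 = -0.1665 at s = 10%, to -0.185 × 0.50 = -0.0925 at s = 50%.
- N = 1.0: -0.333 to -0.185.

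This is dilution with the sign unchanged.

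*Between arms, unequal r, s = 0.* The added bias is -D0 × (r in varnish - r in control). For a 10-point gap this is ∓0.20.

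- 30% varnish, 20% control: -0.185 - 0.20 = -0.385 (N = 0.5); -0.37 - 0.20 = -0.57 (N = 1.0).
- 20% varnish, 30% control: -0.185 + 0.20 = +0.015 (N = 0.5); -0.37 + 0.20 = -0.17 (N = 1.0).

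A modest gap can matter because clearance acts on the whole existing stock, while varnish acts on one year's new lesions.

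**4. Would DMFT alone be enough?** It would keep filled and extracted teeth in the count. It would not deal with shedding, since teeth missing for other reasons are not part of the index. A tooth-level increment deals with both.

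**The case against.** A reader might infer that decayed teeth is the trial's continuous caries outcome and that it measures treatment and shedding instead of prevention. The text does not support that. The count is introduced as an example of a data type, and it is neither the primary outcome nor a listed secondary one. New decay still raises it. The comparison is randomized and adjusted for age and baseline oral health, and equal clearance of baseline decay leaves the difference between arms where it should be.

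A reader might also infer that the month-6 examination in the varnish arm makes the result favour varnish. That examination is described only as an eligibility check. No referral or treatment following it is described, and both arms receive the baseline examination and the same education. Unequal clearance is therefore possible, but the documents do not show that it will occur or in which direction.

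It can further be said that deriving a non-primary count is normally left to a fuller document. That would answer a missing definition. It does not answer the choice of an unsuitable variable in the sentence on evaluating effectiveness, when no increment is named for analysis anywhere in the article.

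Finally, the replacement needs care. Table 1 has no code for an unerupted tooth (eruption stage starts at one-third), and a rule restricted to sound teeth would miss new decay on a tooth already filled. Both points stand and are handled in the fix.

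**Conclusion.** The point holds in a limited form. The decayed-teeth count is a poor choice of example for a prevention trial, because over 12 months it mixes new caries with treatment and tooth loss. Paired within-group comparisons would be hit hardest if this count is used in them, since no control arm cancels the clearance. For the randomized comparison, the expected consequence is dilution if new lesions are treated equally in both arms. Bias arises only if clearance differs between arms: with 2 decayed teeth at baseline, a 10-point gap moves the estimate by 0.20 teeth either way, against a true effect of 0.185 to 0.37. These sizes rest on assumed baseline decay, new lesions and clearance. What does not depend on them is that the count can fall with nothing prevented.

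The binary primary outcome and the sample size are unaffected. This is an inexpensive improvement to make before analysis, which the article says has not begun.

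**What to change.** In the Statistical Analysis section, replace the decayed-teeth example with a 12-month new-caries increment per student, derived from the tooth-level codes and computed separately for primary and permanent teeth:

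- Count teeth that were coded A at baseline, or were not recorded as present at baseline and had erupted by follow-up, and that are coded B, C, D or E at 12 months.
- State whether a change from D to C (new decay on a filled tooth) counts as new caries.
- Teeth coded X at follow-up leave the risk set and are not counted as improvement.
- Report the decayed, missing and filled components descriptively by arm, so that any difference in treatment between arms is visible.

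The cost is a little programming on data planned for collection at both examinations, including a rule for teeth that erupt during follow-up. The downside is that teeth shed before month 12 contribute no outcome.

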### Stratification, Randomization, and Allocation Concealment

Guangzhou, representing a high economic development region within the Pearl River Delta along with Yunfu and Heyuan, which represent middle-to-low development regions from western and northern Guangdong, respectively, were purposively selected to ensure geographic and socioeconomic diversity. Within each of these 3 cities, eligible schools were identified from lists of schools willing to participate provided by local education authorities. School-level cluster randomization was then performed stratified by city. A computer-generated random allocation sequence was produced by an independent statistician who was not involved in school recruitment, baseline assessment, or intervention implementation. Schools within each city were randomly assigned to either the intervention or control group according to this sequence. To ensure allocation concealment, opaque, sealed envelopes containing group assignments were prepared by staff not involved in intervention implementation. Allocations will be disclosed only after completion of school enrollment. Ultimately, 5 control schools and 7 intervention schools were selected across the 3 cities to participate in the study (Figure 1).

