### Strengths and Limitations

This study uses a stratified cluster RCT design, enhancing internal validity and allowing for robust comparisons across different economic regions. The FV intervention is evidence-based and feasibly integrated into the school setting, facilitating scalable and routine implementation for high-risk populations. Standardized assessment tools and trained personnel are used for oral health examinations and data collection, ensuring measurement consistency and data quality.

Despite these strengths, several limitations should be considered. As the study is conducted within schools, findings may not be generalizable to children with disabilities who are not enrolled in special education institutions.

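### Schools were randomised within city, but city is not named in the primary model, and regional subgroups of 12 schools cannot serve as a robustness check

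*Protocol article*

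**What the plan says.** Under Stratification, Randomization, and Allocation Concealment, three cities were chosen purposively to differ in economic development: one high, two middle-to-low. "School-level cluster randomization was then performed stratified by city". The result was 12 schools: "Ultimately, 5 control schools and 7 intervention schools were selected across the 3 cities to participate in the study". The readable text does not give the split within each city.

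The abstract describes the stratifier differently: "Schools will be stratified by regional economic development level and randomly assigned".

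Under Statistical Analysis, "mixed-effects logistic regression will be used for binary outcomes, such as caries presence", and "Models will adjust for relevant covariates, including age, sex, socioeconomic status, and baseline oral health status". On clustering: "Cluster effects will be accounted for using robust SEs or multilevel modeling, as appropriate". Neither sentence mentions the stratification. Region enters the analysis once: "Sensitivity analyses, including subgroup analyses by economic region, will be conducted to assess the robustness of the findings". Strengths and Limitations then says of the design that it is "allowing for robust comparisons across different economic regions".

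**The concern.** City is a design variable twice over. It defines the randomisation strata, and the cities were picked because they differ in a way likely to be related to caries. An analysis that ignores such a stratifier leaves between-city variation in the between-school error term, although the within-city randomisation largely removed it from the comparison of arms. The reported standard error is then larger than the true one, the interval too wide and the test conservative. Where the allocation ratio differs between cities, city differences also leak into the treatment estimate.

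The stratifier is described in two ways. City has 3 levels; economic development, as the Methods use it, could have 2. A reader cannot tell which term a stratified analysis should carry.

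Finally, regional subgroups are offered as a check of robustness, and the Discussion treats regional comparison as a strength. Each region holds only a few schools, so a non-significant regional result could be misread as inconsistency, or a similar one as confirmation.

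**Working it through.** **1. The plan's own figures.** From Sample Size: p1 = 0.60, p2 = 0.40, z-values 1.96 and 1.28, cluster size 150, ICC 0.02, dropout 10%.
- n = (1.96 + 1.28)² × (0.24 + 0.24) / 0.20² = 125.97, so 126 per group.
- Design effect = 1 + 149 × 0.02 = 3.98; 126 × 3.98 = 501.5, stated as 501.
- 501 / 0.9 = 556.7, so 557 per group and 1114 in total.

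These reproduce. They do not depend on whether city is in the model.

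**2. Can the arms be balanced within every city?** Equal ratios need 7/12 of the schools in each city to be intervention schools. As 7 and 12 share no factor, each city would need a multiple of 12 schools, and there are 12 in all. Some association between arm and city is therefore unavoidable.

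**3. Precision if the total ICC is the stated 0.02.** Analysed students per school: 1114 / 12 × 0.9 = 83.55. Variance of a school mean: 0.24 × (1 + 82.55 × 0.02) / 83.55 = 0.00762. SE of the arm difference: √[0.00762 × (1/5 + 1/7)] = 0.051. With 10 df, power for 20 points is 94%. Adding city leaves 8 df and a residual ICC of 0.02 × (1 − share), where share is the assumed part of between-school variance due to city (arm–city imbalance ignored):

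| Share due to city | SE with city | 95% CI half-width (0.114 without city) | Power (94% without city) |
|---|---|---|---|
| 0% | 0.051 | 0.118 | 93% |
| 25% | 0.047 | 0.108 | 96% |
| 50% | 0.042 | 0.098 | 98% |
| 75% | 0.037 | 0.086 | 99.6% |

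At an assumed ICC of 0.05, power is 72% without city and 69%, 79%, 89% and 97% with it.

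**4. Simulation with larger city differences.** Assumptions: within-city ICC 0.02 (beta-binomial), 83 students per school, per-city split 3:2, 2:2, 2:1 (intervention:control), school-level linear model with no other covariates, true effect 20 points.

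| Assumed city prevalences | Type I error without / with city | Power without / with city | Mean CI width (null) without / with city |
|---|---|---|---|
| 50/60/70% | 0.8% / 5% | 73% / 92% | 0.32 / 0.23 |
| 55/60/65% | 3% / 5% | 89% / 92% | 0.25 / 0.23 |
| 60/60/60% | 5% / 5% | 94% / 92% | 0.22 / 0.23 |

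The first row implies more clustering than the plan assumes. Weighting cities by 5, 4 and 3 schools, the mean prevalence is 0.583 and the between-city variance 0.00639. The within-city school variance is 0.02 × 0.2367 = 0.00473. Total ICC = (0.00639 + 0.00473) / (0.583 × 0.417) ≈ 0.046, over twice the stated 0.02.

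**5. Shift of the estimate.** With no treatment effect and prevalences 50/60/70%:
- Split 3:2, 2:2, 2:1: intervention mean (3×50 + 2×60 + 2×70)/7 = 58.6%, control mean (2×50 + 2×60 + 1×70)/5 = 58.0%. Shift +0.6 points.
- Split 4:2, 2:1, 1:2: (4×50 + 2×60 + 1×70)/7 = 55.7% against (2×50 + 1×60 + 2×70)/5 = 60.0%. Shift −4.3 points, in favour of varnish.

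With city in the model the shift is zero in both. In the uneven split power is similar (92% without city, 91% with), so the gain there is an unshifted estimate. If cities do not differ, adding city in that split costs 94% to 90% power.

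**6. The region question.** Take two regions of 6 + 6 schools (assumed 3:3 and 4:2) at ICC 0.02. SE of the difference in effects: √[0.00762 × (1/3 + 1/3 + 1/4 + 1/2)] = 0.104. With 8 df, power is about 40% for a 20-point difference in effect and 14% for 10 points; the difference detectable with 80% power is about 33 points. For 4 + 8 schools (2:2 and 5:3) the figures are 37%, 13% and about 35 points.

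**The case against.** The strongest reply is that the covariate list is introduced as examples. City is not excluded, this is a condensed article, and a full covariate list often sits in an analysis plan that is not shown. That stands: a reader might infer that the primary model leaves city out, and the document does not say so. What remains is that the article names four covariates, omits the one fixed by the design, and describes that factor in two ways.

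Second, the largest power loss does not describe the planned analysis. Caries experience measured by DMFT is largely cumulative, so the planned adjustment for baseline oral health, together with socioeconomic status, should absorb much of any stable city difference. In a simulation of the 50/60/70% case with school baseline prevalence added and city left out, power was 98% if school effects were assumed stable over the year and 79% if they were unrelated between visits apart from city. That scenario also exceeds the stated ICC. So 73% is a pessimistic illustration, and a reader should not take it as the trial's power. If cities do not differ, adding city costs a little power.

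Third, a reader might infer that the regional subgroups are separate models, or that the missing term is why the region question cannot be settled. The text does not say how the subgroups are fitted, and an interaction would be compatible with it. The two lower-development cities may also form one region. The limit comes mainly from having 12 schools. This objection stands, but it supports calling the regional analysis exploratory.

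**Conclusion.** The point holds as a matter of specification. Randomisation was stratified by city, and the primary model as described does not name city. The consequence is conditional: only if cities differ in caries after adjustment for socioeconomic status and baseline oral health are standard errors too large and the test conservative. The unequal allocation ratio across cities is then also a route to a shifted estimate.

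The size cannot be fixed from the document. Across the covariate-free scenarios with the near-balanced split, including city changes power by anything from a loss of 2 points to a gain of about 19. At the planned ICC of 0.02 in total, power is about 94% even without city. City prevalences, per-city splits, the share of variance due to city and ICCs other than 0.02 are all assumptions.

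Separately, regional subgroups of this size cannot show robustness, whatever model is fitted. The primary comparison is not invalidated, but the change should be made, and with analysis not yet started it can still be prespecified.

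**What to change.** - Name city as a 3-level fixed effect in the primary model and in the secondary-outcome models. Any permutation test should permute within city.
- Align the abstract with the Methods so that both give city as the stratifier, and state the number of schools per arm in each city.
- Replace regional subgroups as a robustness check with one arm-by-region interaction, reported as an estimate with its confidence interval and labelled exploratory. Define region (two or three levels) in advance.
- Soften the statement on regional comparisons in Strengths and Limitations.

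The cost is one model term using 2 of the 10 between-school degrees of freedom, plus wording. If cities turn out not to differ, power falls from about 94% to between 90% and 93%, depending on the split. No change to recruitment, schools or data collection is needed.
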